## Abstract

**Background:**

Back pain is one of the most frequent causes of health-related work absence. In Germany, more than 70% of adults suffer from at least one back pain episode per annum. It has strong impact on health care costs and patients’ quality of life. Patients increasingly seek health information on the internet. However, judging its trustworthiness is difficult. In addition, physicians who are being confronted with this type of information often experience it to complicate the physician-patient interaction. The GAP trial aims to develop, implement and evaluate an evidence-based, easy-to-understand and trustworthy internet information portal on lower back pain to be used by general practitioners and patients during and after the consultation. Effectiveness of GAP portal use compared to routine consultation on improving communication and informedness of both physicians and patients will be assessed. In addition, effects on health care costs and patients’ days of sick leave will be evaluated.

**Methods:**

We will conduct a prospective multi-centre, cluster-randomized parallel group trial including 1500 patients and 150 recruiting general practitioners. The intervention group will have access to the GAP portal. The portal will contain brief guides for patients and physicians on how to improve the consultation as well as information on epidemiology, aetiology, symptoms, benefits and harms of treatment options for acute, sub-acute and chronic lower back pain. The GAP portal will be designed to be user-friendly and present information on back pain tailored for either patients or physicians in form of brief fact sheets, educative videos, info-graphics, animations and glossaries. Physicians and patients will assess their informedness and the physician-patient communication in consultations at baseline and at two time points after the consultations under investigation. Days of sick leave and health care costs related to back pain will be compared between control and intervention group using routine data of company health insurance funds.

**Discussion:**

The GAP-trial intends to improve the communication between physicians and their patients and the informedness of both groups. If proven beneficial, the evidence-based and user-friendly portal will be made accessible for all patients and health professionals in back pain care. Inclusion of further indications might be implemented and evaluated in the long term.

**Trial registration:**

German Clinical Trials Register DRKS00014279 (registered 27th of April 2018).

**Electronic supplementary material:**

The online version of this article (10.1186/s12875-019-0925-8) contains supplementary material, which is available to authorized users.

## Background

The GAP trial will compare the communication of general practitioners and patients in consultations using an evidence-based, up-to-date, and independent internet portal in plain language with the communication in usual consultations without the use of the internet portal. The acronym GAP stands for the German words for “well informed physicians and patients”. In English it stands for **G**eneral practitioner **A**nd **P**atient communication. The study will evaluate the effects on physicians’ and patients’ perception of being well informed, the patients’ participation in the consultation, and the quality of the physician patient communication.

Both patients and physicians identified the lack of easy-to-understand and easy-to-use information resources as a barrier to well informed health decisions [1]. Barriers reported by physicians are (1) availability of scientific publications in English only, (2) complicated and expensive accessibility of e-journals and databases, and (3) lack of time to obtain the information, especially at the point of care and during decision-making [2].

The majority of globally generated evidence syntheses on effects of health care interventions are only available in English [3–5]. Accordingly, possible benefits and risks are often not sufficiently communicated at the point of care [6]. Patients may often barely understand information material, even when written in their native language. Consequently, they might not be able to informedly participate in medical consultations and shared decision-making [7–9].

In addition to face-to-face medical consultations, patients seek health information on the internet [10]. However, internet sources can hardly be appraised by patients [11–13]. Physicians sometimes experience internet information as irritating for the physician-patient relation and communication, thereby affecting the treatment outcome.

Back pain was chosen as medical condition of investigation because of its high burden of disease, its substantial impact on patients’ quality of life, and its relevance for public health [14]. The one-year prevalence account for more than 70% in Germany [15]. Chronic back pain is one of the most frequent causes for sick leave and early retirement, and related health care costs: Patients with back pain insured by company health insurance funds (BKK) were on sick leave due to back pain for 1700 days per 1000 insured persons and annum [16].

The optimal treatment strategy for back pain is controversial and approaches differ considerably between medical specialties, institutions and regions. The average cost for back pain treatment is 1322 € per patient and year, with 46% being direct costs for health care [17]. The German Council of medical experts reported over-, under- and misuse of care in back pain [18]. Adherence to clinical guidelines is low [19–21], and better coordination of back pain care may reduce the high costs of chronification [22].

In order to synthesize the evidence in the field of interest, we analysed Cochrane systematic reviews on generic and specific interventions to improve either medical consultation in general or health decisions in back pain.

• Dwamena and colleagues [23] reviewed 43 RCTs regarding the improvement of patient-centred medical consultations in primary care and concluded that training can increase physicians’ and nurses’ skills in patient-centred counselling. However, effects on patients’ health status, behaviour and satisfaction with consultation remained unclear. Evidence indicates that complex interventions addressing both patients and health professions might be more effective. Further research is necessary to confirm this hypothesis.

• A review on shared decision-making including 38 RCTs and one CCT revealed only 3 doublets with the review of Dwamena et al. and comes to congruent conclusions. Evidence quality is low but indicates that involving patients and health professionals may be more efficacious than addressing only one group [24].

• A review of 65 RCTs on patients, who were asked to give informed consent to surgery or other invasive interventions, showed that the use of written or audio-visual information material increased the patients’ knowledge about the planned interventions and reduced decisional conflicts [25]. The use of the information material showed no effects on generalized anxiety or anxiety with the consent process.

• Car and colleagues [26] assessed interventions for enhancing consumers’ online health literacy. In one RCT with HIV patients, internet health information classes improved (1) the self-efficacy for health information seeking, (2) health information evaluation skills, and (3) the number of times the patient discussed online information with a healthcare provider. In one CCT with healthy adults aged 50+, training improved the readiness to adopt the internet as tool for preventive health information. The review authors concluded that well-designed RCTs with various user-groups and 1-year-follow-up assessment are needed.

• A review of 24 RCTs on interactive applications for health communications in patients with chronic diseases revealed that knowledge, self-efficacy, social companionship, health behaviour and clinical outcomes were improved by interactive applications including an information portal combined with additional support either for decision-making, behaviour change or social support [27]. These findings, however, should be confirmed by well-designed RCTs.

• Engers et al. [28] reviewed 24 RCTs on individual education of patients with back pain. They found positive effects on return-to-work by intensive individual patient education in people with subacute back pain, but no effects of low frequent education and on long-term pain reduction. For chronic back pain, individual education was less effective for back pain-specific function when compared to more intensive interventions.

• A review on professional interventions for general practitioners on the management of musculoskeletal conditions analysed 10 trials on back pain [29]. Dissemination of and education on guidelines did hardly or not improve the generals practitioners’ adherence to guidelines. The combination with feedback on the total number of investigations or reminders attached to radiology reports reduced the number of investigation requests.Summarizing these evidence syntheses, we conclude that (1) interventions for the improvement of shared decision-making and patient-centred communication should address both general practitioners and patients, (2) written or audio-visual material and interactive e-health applications may improve patients’ knowledge, decision-making and self-efficacy, (3) knowledge about successful use of internet sources for finding health information in general and in back pain specifically is limited, and (4) intensive education of patients and specific feedback for general practitioners is necessary in order to change patient behaviour or to reduce the number of diagnostic requests in back pain.

As evidence is still not optimally used for evidence-based decision-making at the point of care in primary care consultations, the GAP-trial intends to develop, implement and evaluate an easy-to-understand and easy-to-navigate health information internet portal for general practitioners and patients. Benefits of primary care consultations using the portal (intervention) and not using it (control: consultation as usual) will be compared in patients with back pain.

## Methods

The GAP trial uses a prospective multi-centre, cluster-randomized parallel group design in order to evaluate whether the use of the GAP portal on back pain is superior to routine care. The GAP project consists of three phases. (1) Within the pilot phase, the portal will be tested for usability by physicians and patients and adapted according to the pilot findings (Additional file 1: Development and piloting of the GAP portal). (2) The main trial (second phase) evaluates the effects on pre-defined outcomes in general practitioners and patients with back pain (Table 1). (3) Within the third phase, the potential benefit of web-based information for health problems other than back pain will be analysed (Additional file 2: Expanding of the GAP portal).

**Table 1 Tab1:** PICO question of the GAP trial

Research Question	What are the effects of using the back pain internet portal compared to standard care in patients with back pain?
Population	150 general practitioners and 1500 back pain patients in Northern Bavaria
Intervention	Using the portal during (physician) and after (patient) the consultation.
Comparison	Routine consultation (no use of the portal)
Outcomes	1. Physicians‘and patients’ informedness 2. Physician-patient-communication 3. Patients‘health literacy and self-efficacy expectation 4. Days of sick leave 5. Back pain related health costs

*Hypothesis on primary outcomes:* (1) After the consultation, the informedness and the quality of the physician-patient communication are rated significantly higher by general practitioners and patients who use the portal (intervention group, IG) than by those who do not (control group, CG, consultation as usual).

*Hypotheses on secondary outcomes:* (2) 3 weeks after the consultation, the patients’ informedness, health literacy and self-efficacy are significantly higher among those who use the portal than among those who do not. (3) 3 months after consultation, the number of days of sick leave as well as the utilization of health system resources is significantly lower among patients who use the portal than among those who do not.

*Design:* Prospective cluster RCT with pre-, post- and one follow-up-measurement and process evaluation.

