### Outcomes

*Primary outcomes,* which are assessed by questionnaires (survey data), are the quality of the patient-physician communication and patient informedness (Table 2). It is analysed whether values in the IG differ significantly from the CG.

**Table 2 Tab2:** Primary outcomes, instruments and measurement points

	t_0-physician_	t_0-patient_	t_1-patient_	t_2-patient_	t_1-physician_	t_2-physician_
Quality of the patient-physician communication (patient)						
Shared Decision-Making Questionnaire (SDM-Q-9) [38]			X			
Questionnaire on the communication behaviour of physicians (KOVA) [39]			X			
Scale “Satisfaction” of the P.A.INT-questionnaire [40–43]			X			
Quality of the patient-physician communication (physician)						
Scale “Effective and open communication” of the KOVA [39]^a,b^	X				X	X
Scales “Empathy”, “Openness and coherence”, “Positive regard and appreciation”, “Contact barriers” and “Satisfaction” of the P.A.INT-questionnaire [40–43]^a^	X				X	X
One Item of the Man-Son-Hing scale. [44]^a^	X				X	X
Shared Decision-Making Questionnaire (SDM-Q-Doc) [45, 46]^a^	X				X	X
Informedness (patient)						
Self-reported knowledge questionnaire^c^		X		X		
Self-reported knowledge global question^c^			X			
Perceived informedness questionnaire^c^				X		
Perceived informedness global question^c^			X			

^a^Instruments will be adapted so that physicians assess their communication behaviour across consultations

^b^Instrument will be adapted for assessing the communication from physician’s perspective

^c^These instruments will be developed for the project. The questionnaires will be checked for understandability and acceptance in a cognitive pretest using one-to-one interviews with eight patients having experienced back pain [47]

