*Secondary outcomes* are assessed by questionnaires (survey data) and routine data from the insurance companies (Table 3). Secondary patient outcomes are self-reported self-efficacy regarding their own communication behaviour, health literacy, pain intensity, and days of sick leave and back pain related costs for the health care system. Since t0 and t1 of the patient survey are close together, outcomes of informedness, self-efficacy, and health literacy at t1 are only assessed via global questions. Secondary outcomes for physicians in the IG are the concordance of provided and needed information, the usability of the platform and their actual use of it. Correlation of physician and patient data is possible, as the used items and questionnaires are similar. Differences between CG and IG are additionally analysed regarding the secondary outcomes. Table 3 also contains additionally assessed variables.

**Table 3 Tab3:** Secondary outcomes and control variables

	t_0-physician_	t_0-patient_	t_1-patient_	t_2-patient_	t_3-patient_	t_1-physician_	t_2-physician_
Secondary outcomes (survey data)							
Self-reported self-efficacy (patient)							
Perceived Efficacy in Patient-Physician Interactions (PEPPI)-Questionnaire [48]		X		X			
One Item of Perceived Efficacy in Patient-Physician Interactions (PEPPI)-Questionnaire [48]			X				
Health Literacy (patient)							
Health Literacy Questionnaire (HLQ) [31, 49]		X		X			
Health literacy global questions			X				
Pain intensity (patient)							
Visual analog scale (VAS) [50]		X		X			
Accordance of provided and needed information (physician)							
Domains “Adequacy of information” and “Usability of information” of the Decision Attitude Scale^a,b^ [51]						X	
Self-developed item whether content fits expectations						X	
Usability (physician)							
System Usability Scale (SUS)^a,b^ [52]						X	
Self-developed items on usability						X	
Use of portal (physician)							
Self-developed items on actual use of portal^b^						X	X
Secondary outcomes (routine data)							
Patient’s days of sick leave					X		
Patient’s back pain related costs for the health care system					X		
Control variables (survey data)							
Patient							
Back Belief Questionnaire [53]		X					
Sociodemographic data		X	X	X			
Internet Use		X					
Medical data		X		X			
Physician							
Sociodemographic data	X						
Structural features of the practice (kind of practice, patients per quarter, number of employees, location and region)	X						

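### The primary informedness endpoint is not fixed: three-week patient informedness is secondary in the hypotheses but primary in Table 2, and GP informedness is hypothesised without an instrument

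*Protocol article*

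**What the plan says.** **Time point.** In Methods, Hypothesis 1 (primary) states that after the consultation "the informedness and the quality of the physician-patient communication are rated significantly higher by general practitioners and patients who use the portal". Hypothesis 2, under the secondary outcomes, states that "3 weeks after the consultation, the patients’ informedness, health literacy and self-efficacy are significantly higher among those who use the portal". Procedures for patients defines t1 as the questionnaire completed in the practice after the consultation, and t2 as the postal questionnaire three weeks later.

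**Instruments.** Table 2, headed as the table of primary outcomes, has four patient informedness rows:
- self-reported knowledge questionnaire, at t0 and t2;
- self-reported knowledge global question, at t1;
- perceived informedness questionnaire, at t2 only;
- perceived informedness global question, at t1.

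The paragraph on secondary outcomes adds that "outcomes of informedness, self-efficacy, and health literacy at t1 are only assessed via global questions". Table 3 contains no informedness row. The section on patients' questionnaire data plans separate multilevel models at t1 and t2 and names neither as primary.

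**Whose informedness.** The PICO table lists "1. Physicians‘and patients’ informedness" as its first outcome, and the abstract promises both. The Outcomes section says that the primary outcomes "are the quality of the patient-physician communication and patient informedness".

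**Error rate.** The sample size section splits 5% over two primary outcomes, 2.5% each.

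**The concern.** A primary endpoint needs one measure at one time point, fixed in advance. Here the hypotheses say that three-week patient informedness is secondary, and Table 2 says that it is primary. If t1 and t2 gave different answers, one part of the article would support saying that the primary aim was met and another that it was missed. The Blinding section states that evaluators cannot be blinded, so a choice made after the data are in would be made by people who know the allocation.

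The GP part is a different problem. A claim about GPs' informedness stands in the primary hypothesis, but if nothing measures it, the trial can neither confirm nor refute it.

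**Working it through.** **1. The plan's own figure.** Inputs from the sample size section: effect size 0.30, power 0.80, alpha 2.5% per primary outcome, 2:1 allocation. Sidedness is not stated. With a two-sided test,

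n(CG) = (1 + 1/2) × (2.241 + 0.842)² / 0.30² = 158.4, so 159 in the CG and 318 in the IG.

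This matches the stated 160 and 320. One-sided 2.5% gives 131 and 262 and does not match. The stated figures times the design effect of 1.09 give 348.8 and 174.4, stated as 349 and 175. Dividing by 1 − 0.35 gives 537 and 270. The plan's numbers are therefore sound for one two-sided test at 2.5% in each of two domains.

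**2. How many informedness tests carry the primary label.** Table 2 gives two measures at t1 and two at t2, four in all. No composite or order is stated. The health-economic section treats knowledge and perceived informedness as separate quantities, with a cost-effectiveness ratio for each.

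**3. Error for the informedness domain if any one of the four may be chosen.**
- One fixed test: 2.5% two-sided, 1.25% in the direction of benefit.
- Four independent tests, either direction: 1 − 0.975⁴ = 9.6%. This is an upper bound.
- Four independent tests, benefit only: 1 − 0.9875⁴ = 4.9%.
- Four correlated tests: the article gives no correlations. With assumed common pairwise correlations of the test statistics of 0.3, 0.5 and 0.7, simulation gives about 9.1%, 8.3% and 7% two-sided, and about half of each for benefit.
- Only the two t1 items, as Hypothesis 1 implies: 1 − 0.975² = 4.9% two-sided at most.

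**4. Is patient number a problem?** No. The target of 1000 and 500, after 35% dropout, leaves 650 and 325. With the design effect of 1.09, power at d = 0.30 is about 98% at the 2.5% level, and about 96% even if alpha were divided over four tests (1.25% each).

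**5. Physician informedness, row by row.**
- Table 2, physician rows: KOVA scale, P.A.INT scales, one Man-Son-Hing item and SDM-Q-Doc, all grouped under communication quality.
- Table 3, physician rows: accordance of provided and needed information, usability, and portal use. These are secondary. The accordance scale is footnoted as rating the portal in the intervention group only, so it gives no between-arm comparison of informedness.
- Neither table has a physician informedness row. Reading Hypothesis 1 as GPs rating their patients' informedness does not help, because no such instrument is listed either.

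**The case against.** The strongest reply is that the time point is not open. The hypotheses are the only text that ranks the two occasions, and they put the consultation first and three weeks second. Table 2 could then be read as a schedule of every occasion on which a primary construct is measured. The article also explains why t1 uses global questions: t0 and t1 lie close together. Much of this stands. It would be wrong to infer that the article gives no ranking, and choosing t2 afterwards would go against the written hypothesis. But Table 2 does not say that it is only a schedule, one of its primary questionnaires is collected at t2 alone, and Table 3 offers no place for the informedness outcome of Hypothesis 2. Even with t1 accepted, two global items remain. Choosing between them could be left to an analysis plan; the clash between hypotheses and tables could not.

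A reader might also infer that 9.6% is the actual false-positive rate. It is a bound: it assumes independence, although the measures come from the same patients, and it counts differences in either direction.

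A reader might infer that t1 misses half of the intervention. Patients do get their own portal access only after the consultation, but the physician uses portal material during it, and nothing in the article supports a share of one half. Measuring the consultation effect at t1 and later use at t2 is a legitimate design.

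On GP informedness, the Outcomes section already omits it and the physician analysis is described as primarily exploratory, so it does not affect the patient-level result. The additional file on survey instruments is not shown. The mismatch between the primary hypothesis and both outcome tables remains.

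**Conclusion.** The point holds as an internal inconsistency in the definition of the primary endpoint. Three-week patient informedness is secondary in Hypothesis 2 and primary in Table 2, and the analysis section does not settle which governs. The 2.5% allotted to informedness fits a single test, while four measures carry the label. The possible two-sided error for this domain runs from 2.5%, if one measure is fixed, to at most 9.6%, if any of four independent ones may be chosen. For a false claim of benefit the range is 1.25% to about 4.9%. Positive correlation lowers both upper ends. These figures assume two-sided testing, which is the reading that reproduces the plan's sample size.

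GP informedness cannot be tested as the article stands. This weakens the primary hypothesis as worded, not the patient comparison. The sample size is not in question, and the documents do not show that t2 is the only correct primary time point.

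**What to change.** Before data are analysed, name one patient informedness measure at one time point as primary at the 2.5% level and label the others secondary. Then align Hypotheses 1 and 2, the Outcomes text and Tables 2 and 3. Either choice resolves the conflict:
- **Keep t1**, as Hypothesis 1 has it: name one global item as primary and move the t2 informedness rows to the secondary table. This keeps the stated ranking, but the primary result rests on a global question without a baseline.
- **Choose t2:** the self-reported knowledge questionnaire adjusted for its t0 value, with informedness taken out of Hypothesis 2. It is the only informedness instrument with a baseline, and it follows patients' own portal access. It reverses the ranking in Hypothesis 1.

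Remove GP informedness from Hypothesis 1, Table 1 and the abstract's aim unless an instrument for it already exists. If one does, list it, and treat the result as exploratory: with an assumed 100 against 50 independent GPs, d = 0.30 and 2.5%, power is about 31% before dropout.

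Cost: more than rewording. A change to the primary endpoint is a change to the evaluation, to be documented and reported as the Protocol amendments section requires. If t2 is chosen, postal dropout may be higher than at t1. The 35% allowance, and a target of 1000 and 500 against the 537 and 270 needed, should absorb it.
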